### Study organization and quality control

The principal investigator, study coordinators, and the Office of Scientific Research at West China Hospital are jointly responsible for all aspects of the study protocol and relevant amendments. The implementation of the study, data completeness, and accuracy will be supervised by the Department of Anesthesiology, West China Hospital. The data safety and monitoring board (DSMB), including an orthopedic surgeon, an anesthesiologist, a statistician, a physician, and a member from the Office of Scientific Research who are not unrelated to this trial, will be involved for the entire duration of the trial to review all investigational data for accuracy and completeness periodically to ensure protocol compliance, and to make the decision to stop the trial if there are abnormal frequencies of safety issues, or if the safety of a participant was not guaranteed because of serious complications. [name], associated professor of Department of Anesthesiology, West China Hospital, will be the personnel to alert serious complications to the DSMB and be responsible for site monitoring. Data collection and follow-up will be performed by clinical research coordinators. There will be no preliminary analysis performed before the completion of the study.

### Enrollment criteria

#### Inclusion criteria

Patients undergoing primary TKA and THA, of both gendersAge > 18 yearsAble to communicate, particularly the ability to express and totally understand an informed consent

#### Exclusion criteria

Refusal to sign consentPregnancy or lactating female patientsHistory or family history of malignant hyperthermiaKnown allergy to propofol, desflurane, or any other anesthetic agentHistory of substance abuseHistory of postoperative deliriumImpairment of cognitive function or communicationPsychopathyActive participation in another trial where the primary endpoint follow-up is ongoingUnwillingness or inability to comply with protocol procedures

### Interventions

#### The ERAS group

Patients will be treated according to the ERAS pathway, which is elaborated below.

ERAS pathway for orthopedic surgeons:
Preoperative fasting time: 8 h for consumption of fats and protein food, 6 h for starchy food or non-human milk, and 2 h for clear liquids before operation.Intravenous 20 mg/kg of tranexamic acid will be given 15 min before incision.No indwelling urine catheters.No tourniquet used for TKA.No drainage tube after surgery.Give low molecular heparin subcutaneously 6 h after the operation.

ERAS pathway for anesthesiologists:
Before anesthesia induction, ECG, non-invasive blood pressure, pulse oximetry, and capnogram will be continuously monitored for every patient.Intravenous 10 mg of dexamethasone immediately before anesthesia induction.Anesthesia will be induced with 0–0.2 μg/kg of sufentanil or 0–2 μg/kg of fentanyl, 0.3 mg/kg (for THA) or 0.15 mg/kg (for TKA) of cis-atracurium, and 1 mg/kg of propofol. Endotracheal intubation of insertion or laryngeal mask will be performed when the BIS value decreases to 50.Anesthesia will be maintained by titrating continuous remifentanil infusion at a range of 0.15–0.3 μg/kg.min with continuous infusion of propofol of 2–4 mg/kg/h, or keeping end- tidal desflurane (Et-Des) level at 5–7% or sevoflurane (Et-Sev) level at 1.5–2.5%. The BIS value will be kept in the range of 40–60 during the procedure.Incision site will be infiltrated with 40–50 mL of 0.2% ropivacaine at the end of the operation for postoperative analgesia; no patient-controlled intravenous analgesia devices will be applied postoperatively.

#### The non-ERAS (Control) group

Patients undergoing THA or TKA will receive conventional care according to the individual participating center. There is no standard protocol for preoperative management, including fasting guidelines, no restriction of choices of anesthetic techniques and intraoperative medications, as well as postoperative analgesia, and indwelling urinary catheter.

For all the individuals enrolled in the study, no matter which group they are allocated, the decisions regarding whether to place the urinary catheter or drainage tube, or to use tourniquet, or to perform any other medical treatment should be made by the individual responsible physician, based on his clinical judgment. For example, if a patient is allocated to the ERAS group, but he develops urinary retention perioperatively as a result, the urinary catheter could be retained. In such case, we will make a record, and the patient will still be followed up and his data will be collected and analyzed in the ERAS group as per other individuals in the same group.

### Outcome measures

#### Primary outcome

The primary outcome is LOS in hospital, which is defined as the time frame from the day of hospital admission to discharge from the hospital (unit: days).

#### Secondary outcomes

i.Postoperative LOS, which is defined as the time frame from the day of operation to discharge from the hospital (unit: days).ii.All-cause mortality by 30 days after operation.iii.In-hospital complications, which are divided into five grades:
Grade I: recovery after temporary treatment, e.g. postoperative nausea and vomiting (PONV), postoperative anxiety, insomnia.Grade II: prolonged hospitalization, e.g. pulmonary infection requiring antibiotics or other treatment, surgical wound infection requiring wound debridement.Grade III: life-threatening complications requiring intense treatment during hospitalization and resulting in good functional recovery, e.g. dialysis therapy for acute renal insufficiency, mechanical ventilatory support for respiratory failure, or postoperative bleeding requiring re-operation.Grade IV: life-threatening complications resulting in significantly decreased quality of life, e.g. myocardial infarction, stroke that left paralytic limbs.Grade V: all-cause mortality by 30 days after operation, which is defined as a secondary outcome.iv.Mobilization time, which is defined as the time frame from the end of operation to the ability to walk without external assistance (unit: hours).v.Numerical rating scales (NRS) scores at rest during three days after operation.vi.NRS scores during mobilization or physical therapy during three days after operation.vii.Postoperative sufentanil or other analgesics requirement during three days after operation.viii.Total in-hospital cost.ix.Readmission rate by 30 days after discharge from the hospital.

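### Grade I–IV complications and cost are counted only until discharge, the event ERAS is meant to bring forward, so they do not cleanly support a claim of no increase in complications or cost

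*Protocol article*

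**What the plan says.** All outcome definitions below are in the Protocol article, Secondary outcomes.

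- Complications are "In-hospital complications, which are divided into five grades". Grades I to IV carry no other time limit, so counting stops when the patient leaves hospital.
- The second grade is headed "Grade II: prolonged hospitalization". Its two examples, a chest infection and a wound infection, are each described by the treatment they need.
- The fifth grade is different: "Grade V: all-cause mortality by 30 days after operation, which is defined as a secondary outcome".
- Cost is "Total in-hospital cost".
- Two outcomes look beyond discharge: "All-cause mortality by 30 days after operation" and "Readmission rate by 30 days after discharge from the hospital".

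The primary outcome (Primary outcome section) is the number of days from admission to discharge. The Statistical analysis section compares categorical outcomes by odds ratio and chi-square test, and states no common time window or allowance for time observed. The last paragraph of the Discussion says the trial is to show that ERAS shortens stay with no rise in complications or medical cost.

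**The concern.** The length of the observation window depends on treatment. If ERAS works as hoped, its patients leave earlier and are watched for fewer days. At identical risk they would then have fewer recorded Grade I–IV complications, because anything arising after their discharge, but before the day a control patient would have gone home, is counted in one arm only. Costs incurred after discharge drop out in the same way.

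The heading of Grade II adds a second link. An event graded by whether it prolonged the stay partly restates the primary outcome.

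At stake is the second half of the trial's conclusion. A finding of no increase could appear even if some complications and cost had only moved from the ward to the weeks after discharge.

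**Working it through.** **1. Inputs from the plan** (Sample size calculation section). Mean stay for THA is 10 days (SD 1.5) against 8.6 (SD 1.1). For TKA it is 12.1 (SD 2.1) against 8.9 (SD 1.5). The plan uses the first of each pair as control and the second as ERAS. The arms have 160 patients each within each procedure.

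**2. The plan's own figure.** The plan gives no figure for complications. Its only calculation is the sample size for length of stay, and this confirms how the inputs are used. With n = 2(z_α + z_β)²·SD²/difference², 5% significance, 90% power and the root-mean-square SD:
- THA: difference 1.4, SD 1.315. n = 19 per group two-sided or 16 one-sided, against 17 stated.
- TKA: difference 3.2, SD 1.825. n = 7 two-sided or 6 one-sided, against 7 stated.

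TKA reproduces, and THA does so to within two patients.

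**3. Relative observation time.** THA: 8.6/10 = 0.86. TKA: 8.9/12.1 = 0.74.

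**4. Apparent complication ratio when true risk is equal.** Let f be the share of risk spread evenly over the observed stay, with the rest arising before either arm goes home. Let p be the number of preoperative days, taken as equal in both arms. Then

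ratio = (1 − f) + f × (LOS_ERAS − p)/(LOS_control − p).

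Both f and p are assumptions; the plan gives neither.

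| Procedure | p | f = 1 | f = 0.5 | f = 0 |
|---|---|---|---|---|
| THA | 0 | 0.86 | 0.93 | 1.00 |
| THA | 3 | 5.6/7 = 0.80 | 0.90 | 1.00 |
| TKA | 0 | 0.74 | 0.87 | 1.00 |
| TKA | 3 | 5.9/9.1 = 0.65 | 0.82 | 1.00 |

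**5. The same effect on the planned odds ratio.** Assume a constant hazard and a 20% in-hospital risk in the control arm. The ERAS risk is then 1 − 0.8^r, where r is the ratio of postoperative days. The chance of a falsely significant result in favour of ERAS is Φ[(d − 1.96·SE₀)/SE₁], where d is the difference in risk, SE₀ and SE₁ are the pooled and unpooled standard errors, and there are 160 patients per arm.
- THA, p = 0: r = 0.86, ERAS risk 17.5%, odds ratio 0.85, chance 8%.
- THA, p = 4: r = 4.6/6 = 0.77, ERAS risk 15.7%, odds ratio 0.75, chance 17%.
- TKA, p = 0: r = 0.74, ERAS risk 15.1%, odds ratio 0.71, chance 21%.
- TKA, p = 4: r = 4.9/8.1 = 0.60, ERAS risk 12.6%, odds ratio 0.58, chance 43%.

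With one fixed window and equal true risk, the odds ratio is 1.00 and this chance is 2.5%.

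**6. Early events.** Let the hazard halve every one to two days after operation, with a 30-day risk of 20% and 0 to 4 preoperative days. The in-hospital odds ratio is then 0.86 to 1.00, and the chance of a falsely significant result is 2.5% to 8%.

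**7. What the other outcomes catch.** Mortality has the same 30-day window in both arms. Readmission catches a late complication only if it brings the patient back to hospital, and its clock starts at discharge, so it covers different postoperative days in the two arms. A chest or wound infection treated after discharge without readmission appears in no outcome. Readmissions are counted, but as worded their cost is not.

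**The case against.** The strongest reply is that the plan does look past discharge. Thirty-day mortality has a common window, and 30-day readmission would show shifted complications that are serious enough to readmit. This stands, and it narrows the gap to milder events and to readmission cost.

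The size is also open to challenge. Several of the protocol's examples, such as nausea and vomiting or bleeding that needs re-operation, are plausibly early. The calculation assigns the whole difference in stay to the postoperative period, although the Discussion says preoperative preparation also affects stay. Any preoperative share of the difference would shrink the bias. The calculation also ignores that a complication can itself delay discharge, and it uses a before-and-after contrast from one hospital. All of this stands: the direction is better supported than the size.

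On cost, bed-days avoided are a real saving. Only cost falling after discharge is left out.

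A reader might infer three stronger points that the document does not support:
- *That mobilisation is also cut at discharge.* It is defined as "the time frame from the end of operation to the ability to walk without external assistance", with no stop at discharge stated. How patients without an observed walking time are handled may be left to the analysis plan, and no direction of bias can be shown.
- *That the safety comparison must favour ERAS whatever happens.* The bias needs a real difference in stay, and events or costs that fall between the two discharge times.
- *That Grade V shows the same bias.* "Grade V: all-cause mortality by 30 days after operation" is a fixed window, equal in both arms. Its place in a scale called in-hospital is a labelling inconsistency only.

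**Conclusion.** The point holds for Grade I–IV complications and for cost. Their window closes at an event that treatment is expected to move, and Grade II is headed by a criterion that overlaps the primary outcome. If ERAS shortens stay, the comparisons lean towards ERAS or are neutral, so they do not by themselves support a conclusion of no increase.

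With equal true risk, the apparent complication ratio runs from about 1, if events are early, down to 0.86 (THA) and 0.74 (TKA) if risk is even over the stay with no preoperative days. With three assumed preoperative days the lower values are 0.80 and 0.65. These figures rest on the plan's mean stays and on assumptions about event timing and preoperative days that the document cannot settle. No size can be given for cost.

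Only secondary outcomes are concerned. The primary comparison of length of stay is untouched.

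**What to change.** - Count Grade I–IV complications in both arms from operation to a fixed day 30, in or out of hospital. Readmission is already followed to 30 days after discharge, which falls no earlier than day 30 after operation, so the information can be collected alongside that follow-up and the 30-day mortality check.
- Define Grade II by the treatment required, as its two examples already do, and not by length of stay.
- Add the cost of readmissions up to day 30 to the cost outcome, where billing data are available.

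The cost is a few extra follow-up questions, retrieval of some billing records across eight hospitals, and post-discharge events that are partly self-reported. Readmissions to other hospitals may be costed incompletely. The change is best made before recruitment, because unrecorded post-discharge events cannot be reliably recovered later.

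If this is not feasible, limit the Discussion's conclusion on complications and cost to the hospital stay, and report it together with 30-day readmission. That needs no new data.

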By conducting this study, we hope to introduce the concept of ERAS to surgeons, anesthesiologists, nurses, and other allied health professionals. The ERAS pathway requires contributions from all of them. For the comparison group, there is no specific protocol regarding the conventional standard of care in each center, because we do not need to set up a standard “conventional” process to adjust their clinical practice only to make a comparison group with uniform standards. In contrast, for the ERAS group, the pathway is set up strictly with considerations of various aspects. Therefore, the implementation of this study requires deep understanding of ERAS and good collaboration among surgeons, anesthesiologists, ward nurses, and other allied health professionals.

With the hypothesis that ERAS could reduce the LOS while not increasing complications and in-hospital cost when compared with the current clinical practice, we also focus on whether the ERAS pathway could improve the patient’s quality of life or save medical resources. The outcome is to reflect these areas of interest. The primary outcome is LOS in hospital, which is affected by multiple factors such as preoperative preparation, optimization of patient’s pre-morbidities, perioperative anesthetic management, and in-hospital postoperative complications etc. It is an important index relevant to both patient’s quality of life and medical cost. In addition, hospital LOS is not only one of the most concerned outcomes by physicians, but also an index that governments of different countries are attempting to reduce in order to decrease healthcare costs [23]. Secondary outcomes including 30-day mortality, incidence of in-hospital complications, NRS for postoperative pain, total in-hospital cost, and 30-day readmission rate are all related to our hypothesis. Moreover, we divided the in-hospital complications into five grades to elaborate the severity of complications with a clear statement.

In summary, this trial is designed to test the hypothesis that the ERAS pathway could be superior to conventional clinical practice in reducing LOS without increasing the incidence of complications or medical cost.

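### The in-hospital complication outcome mixes two observation windows, one of which shortens with the treatment effect, and its Grades III and IV are split on two different axes

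*Protocol article*

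**What the plan says.** All of this is in the protocol article.

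- **Secondary outcomes**, item iii, is headed "In-hospital complications, which are divided into five grades".
- Grade III covers "life-threatening complications requiring intense treatment during hospitalization and resulting in good functional recovery". Its examples are dialysis, ventilatory support and re-operation for bleeding.
- Grade IV covers "life-threatening complications resulting in significantly decreased quality of life, e.g. myocardial infarction, stroke that left paralytic limbs".
- The last grade reads "Grade V: all-cause mortality by 30 days after operation, which is defined as a secondary outcome". The same death outcome is item ii of the list.
- The only listed measure of function is item iv: "Mobilization time, which is defined as the time frame from the end of operation to the ability to walk without external assistance". The grades do not refer to it. None of the nine items is a quality-of-life measure.
- **Discussion** says "we divided the in-hospital complications into five grades to elaborate the severity of complications with a clear statement". It closes with the aim of showing shorter stay with no rise in complications or cost.
- **Statistical analysis** compares categorical outcomes by odds ratio and chi-square test, and 30-day mortality by Kaplan–Meier plot and log-rank test.

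**The concern.** Two features of the printed definition cause difficulty.

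The first is the window. One outcome counts death over a fixed calendar period and everything less than death over a period that ends when the patient goes home. The second period is itself what the intervention is designed to shorten. An arm discharged earlier has less time in which an event can be recorded, so its count can be lower although its patients are no safer. The outcome supports the safety half of the trial's conclusion, so a bias towards ERAS would matter there.

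The second is the boundary between Grades III and IV. Both are life-threatening. One is set apart by how well function recovers, the other by loss of quality of life. A patient may have both or neither, and one of the named examples can satisfy both grades. Two careful graders could then disagree while each follows the text.

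**Working it through.** The plan gives no figure for this outcome and sizes nothing on it, so there is none to reproduce. The check sets the definitions side by side and adds some subtraction from the Sample size calculation section.

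**Step 1: windows.** Grades I–IV run to discharge, by the name of the outcome. Grade V runs to day 30 after operation.

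| Event | Grade under the text |
|---|---|
| Stroke in hospital, day 5 | III or IV |
| Stroke at home, day 25 | none |
| Death in hospital, day 5 | V |
| Death at home, day 25 | V, under an in-hospital heading |

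**Step 2: how far the windows differ.** The planning means for total stay run from 8.6 days (THA, later period) to 12.1 days (TKA, 2014). Even if the whole stay were postoperative, the part of the 30-day window after discharge is:

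- at 12.1 days: (30 − 12.1)/30 = 17.9/30 = 60%
- at 8.6 days: (30 − 8.6)/30 = 21.4/30 = 71%

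These are shares of calendar time, not of deaths or complications.

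**Step 3: dependence on the treatment effect.** Taking the planning means as the two arms:

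- THA: 10 − 8.6 = 1.4 days; 1.4/10 = 14%
- TKA: 12.1 − 8.9 = 3.2 days; 3.2/12.1 = 26%

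The Grade V window is 30 days in both arms.

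What this does to the count depends on when events occur, which the article does not say. If every Grade I–IV event came before the earliest discharge, the effect would be 0. If events came at a constant daily rate through the stay (assumption), the recorded count in the ERAS arm would be lower by 14% (THA) or 26% (TKA) through observation time alone. Postoperative events tend to come early, so the upper end is unlikely. The direction favours ERAS throughout.

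**Step 4: Grades III and IV.** Take a myocardial infarction that is treated intensively and followed by good recovery.

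- Grade III rule: life-threatening, intensive treatment in hospital, good recovery. All three are met.
- Grade IV rule: quality of life clearly reduced. Not met.
- Grade IV example: myocardial infarction is named without a qualifier of its own; the words about paralysis attach to stroke. The example is met.

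The patient is Grade III by rule and Grade IV by example. A patient who regains function but has reduced quality of life is also caught by both rules. No collected outcome settles either case.

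**The case against.** The strongest case on the other side has five parts.

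1. **The article is condensed.** The assessor, the time of assessment and detailed grading rules may sit in the full protocol or the planned training manual. This stands, and their absence is not counted here. The mixed window and the two axes are printed definitions, however, and further grading rules would not remove the mixed window.
2. **The infarction example can be read together with its rule**, as an infarction that left reduced quality of life. That is a fair reading. It makes the conflict one of loose wording, but it leaves the two axes and the uncollected quality of life in place.
3. **Few events are at stake.** If 0.5–2% of patients had a life-threatening complication (assumption; the article gives no rate), 160 per arm gives 160 × 0.005 = 0.8 to 160 × 0.02 = 3.2 events per arm. A contrast between Grades III and IV would say little on any scale. This stands and limits the second part of the point, but not the first, which concerns Grades I–IV together.
4. **Blinding.** A reader might infer that unblinded physicians will grade differently by arm. The Randomization and blinding section leaves investigators and responsible physicians unblinded, but it blinds follow-up staff, and the Study organization section gives data collection and follow-up to research coordinators. The article does not say who grades, so arm-dependent grading is not shown.
5. **Quality of life is addressed.** A reader might infer that the stated interest ("we also focus on whether the ERAS pathway could improve the" patient's quality of life) cannot be answered by any listed outcome. The Discussion offers length of stay as an index relevant to it. That is a thin proxy, but the link is stated, and the aim need not be deleted.

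**Conclusion.** The point holds in a limited form. Grades I–IV and Grade V are counted over different windows within one outcome. The window for Grades I–IV would be shorter in the ERAS arm if the trial's own hypothesis is right. The Grade III/IV split uses two axes, and at least one named example fits both grades.

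The shortening of 1.4 days (THA) and 3.2 days (TKA) assumes that the arms resemble the planning means and that the whole reduction is postoperative. The planning means are for total stay, so part of the reduction may be preoperative and the effect smaller. They also compare calendar periods, the later one (for THA) with ERAS in about half of patients, so the difference between arms could be larger.

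Some stronger readings are not supported:

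- That recovery cannot be judged before discharge. The article's own example of a stroke with lasting paralysis is visible by then, and mobilization time does record a functional result.
- That the complication comparison as a whole cannot be reproduced. No ordered severity test is specified, and a comparison of any complication with none does not depend on the Grade III/IV split.
- That debridement at Grade II and re-operation for bleeding at Grade III conflict. Only Grade III requires a threat to life.
- That deaths are double counted. The overlap is declared in the grade itself ("all-cause mortality by 30 days after operation, which is defined as a secondary outcome") and no composite adds the two.

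This is an inexpensive improvement to a secondary safety outcome. The primary analysis and the sample size are untouched.

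**What to change.** - **One window.** Count all grades over 30 days after operation in both arms and drop the in-hospital label. Follow-up already covers this: mortality is collected to day 30 after operation, and readmission to 30 days after discharge, which is no earlier than day 30 after operation.
- **One axis.** Define Grades I–IV by the recorded treatment or organ support that the complication required, instead of by a judgment on recovery or quality of life. Clavien-Dindo is one such scale; any grading from chart facts would serve.
- **Mortality.** Keep 30-day mortality as its own outcome with its existing analysis.

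The cost is a few complication questions at the follow-up contact already planned, plus wording in the protocol, the case report form and the training manual. Results would be less comparable with any earlier local data graded on the present scale. An in-hospital count can still be reported beside the 30-day one if it is labelled as such.
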